### Attachment Style Assessment

Attachment will be assessed using a modified ASI, with questions adapted to be applicable to adolescents. This interview elicits the adolescent’s current state of mind regarding the quality of relational experiences with parents and peers. The ASI determines the adolescent’s ability to access and use social support with 3 confidants (ie, parents and peers). This tool assesses relationship quality, social support, and security of attachment style. Several dimensions (ie, mistrust, constraint of closeness, fear of rejection, self-reliance, desire for company, fear of separation, and anger) were coded to determine the attachment profile as either secure or insecure (ie, enmeshed, fearful, angry-dismissive or withdrawn).

### Parent-Adolescent Interaction Assessment

The quality of the parent-adolescent interaction will be assessed with the French version of the GPACS. The development of the GPACS drew on prior literature describing behavioral manifestations of security, insecurity, controlling behavior, and behavioral disorganization among younger children toward their parents in stressful situations. It has already been used in several studies [77-79]. The GPACS coding system includes the rating of each interaction on 10 5-point scales from 1 (not at all) to 5 (very much). There are 2 positive scales (1) “Collaborative Communication” indexing cooperative goal-corrected partnership and parent/adolescent carefulness; and (2) “Caregiving Validation of Adolescent’s Voice” indexing the caregiver’s support for the adolescent. There are 8 negative scales characterizing 3 subtypes of disorganized interaction (ie, punitive, caregiving/role confusion, and disoriented behavior). These 8 scales are (1) parental punitive behavior (eg, angry, critical or mocking comments about the adolescent); (2) adolescent punitive behavior (eg, angry, critical or mocking comments about the parent); (3) adolescent disoriented-distractible behavior (eg, suddenly stopping in midsentence and “freezing” with hand in midair or pausing abruptly in mi-sentence); (4) parental disoriented behavior (eg, the same as adolescent disoriented behavior); (5) adolescent odd, out-of-context or contradictory behaviors, which may seem disjointed, startling, or inexplicable to an observer (eg, using a forced, high-pitched, or childish tone of voice, shifting into unusual, fantasy-based topics); (6) parent odd, out-of-context behavior (eg, using a forced, high-pitched, or childish tone of voice, wandering around the room, stiff, usually shifting away from the topic); (7) adolescent attempts to manage or take care of the parent or modulate the parent’s behavior (eg, offering guidance, defusing tension with over-bright, entertaining behavior); and (8) parental role confusion (eg, asking for advice on topics typically discussed with partner or other adult).

### Psychological Evaluation

To evaluate psychiatric traits in participants we will use an abbreviated version of the Beck Depression Inventory (BDI) [80], the Spielberger State-Trait Anxiety Inventory (STAI, Forms Y A and Y B) [81], and the Toronto Alexithymia Scale (TAS-20) [82].

#### The Beck Depression Inventory

BDI-II will be used as a depression-screening tool. The BDI-II is a self-assessment instrument with 21 items that assess the presence and severity of depressive symptoms. Each question is scored 0 (symptom absent), 1 (symptom present), 2 moderate symptom), or 3 (severe symptom). The total potential score is 63.

#### The Spielberger State-Trait Anxiety Inventory Forms Y A and Y B

This self-report assessment indicates the intensity of feelings of anxiety; it distinguishes between state anxiety (a temporary condition experienced in specific situations) and trait anxiety (a general tendency to perceive situations as threatening). Responses for the S-Anxiety scale will assess intensity of current feelings “at this moment” from 1 (not at all), 2 (somewhat), 3 (moderately so), to 4 (very much so). Responses for the T-Anxiety scale will assess frequency of feelings “in general” from 1 (almost never), 2 (sometimes), 3 (often), to 4 (almost always). The scale has been standardized in French.

#### The Toronto Alexithymia Scale

The TAS-20 [82] comprises 3 factors to assess difficulties in identifying and describing feelings, which are thought to reflect a deficit in cognitive processing and regulation of emotional states [83].

### Eye-Tracking Measurements

The whole of each picture will be treated as a single area of interest (AOI). Prior to detailed statistical analyses, AOIs will be divided into 4 categories (distress, comfort, joy-complicity, and neutral) and each category will be analyzed separately. Fixations will be defined temporally and spatially, using a pre set minimum fixation duration of 80 milliseconds and a maximum dispersion value of 100 pixels. In order to explore different gaze patterns, various parameters (ie, fixation order, first fixation duration, fixation duration, number of fixations, and entry time) will be analyzed in relation to attachment style.

The mean fixation order of an AOI category will be calculated by averaging the fixation order of each AOI in the same category of pictures. The mean first fixation duration (ms) in the AOI will be calculated by averaging first fixation duration for each AOI in the same category of pictures. The mean duration of a fixation (ms) in the AOI will be calculated by averaging the fixation duration for each AOI in the same category. The mean number of fixations will be calculated by averaging the number of fixations in each AOI category. The mean sum of fixation duration will be calculated by averaging the sums of duration of all fixations in an AOI category. The mean entry time for an AOI will be determined by averaging entry time for each AOI in the same category.

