
### Current Study

This study protocol seeks to examine the effects of IN-OT administration on emotion regulation strategies in insecure adolescents. A reliable protocol is crucially needed in the field of attachment and OT research, if we want to build a solid theoretical background for interpreting OT, before IN-OT can be proposed as adjuvant therapy in insecure adolescents with emotion dysregulation. We hypothesize that IN-OT will promote a “momentary” subjective experience of attachment safety and proximity-seeking in insecurely attached adolescents during dyadic stressful interaction. We suppose that both anxious and avoidant adolescents under treatment will communicate with their parents with more self-disclosure, and will manifest less negative (eg, controlled, hostile, odd) behavior than under the PB condition. We suppose that IN-OT will positively bias parent-adolescent interaction, especially for highly anxious individuals, because it should attenuate their chronic concerns about distress, separation, and abandonment. OT might support parent-adolescent interaction and emotion regulation for highly avoidantly insecure adolescents (often suspicious and defensive), who avoid expressing emotions in the family context. We hypothesize that, in general, insecurely attached adolescents under IN-OT will process attachment-related emotional information in a more accessible and open way compared to PB conditions. Compared to the PB, IN-OT will increase exploration of distress and comfort pictures (eg, first fixation duration; number and duration of fixations). During visualization of distress pictures, IN-OT will attenuate emotional arousal by decreasing neurophysiological reactivity (amplitude of specific skin conductance response, SCR), and should also decrease SCR and decelerate heart rate (HR).

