The main objective is to evaluate the effect of IN-OT on the behavior and discourse of insecure adolescents during a disagreement (stressful situation) with one of their parents. This evaluation will be based on the average score on the scales (4 negative and 1 positive) of the Goal-Corrected Partnership in Adolescence Coding System (GPACS) (personal communication from [name], author of the GPACS). Secondary objectives will be to evaluate the effect of IN-OT versus PB on visual exploration strategies for images eliciting attachment-related emotions (ie, distress and comfort). This characterization will be based on the study of eye parameters (ie, total picture fixation time, and average number of fixations per emotion) assessed by a remote eye tracking (ET) device.

We are conducting a randomized, double-blind, placebo-controlled protocol in which insecure adolescent male participants received IN-OT or PB. The protocol was designed to investigate the effects of IN-OT on emotion regulation strategies, by testing whether attachment anxiety and avoidance moderate the effects of IN-OT during a conflict discussion with a parent, and during the visualization of attachment-related pictures.

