#### Stimuli

The Besançon Affective Picture Set-Adolescents (BAPS-Ado) [75] will be used to elicit attachment-related emotions. The following categories of emotional stimuli will be used: (1) “distress” (n=20), (2) “comfort” (n=20), (3) “joy-complicity” (n=20), and (4) “neutral” pictures (n=20). The first category of pictures is scenes of distress (ie, faces expressing sadness or anguish, or scenes of loss and separation). The second category is comfort-related scenarios (ie, a parent comforting an infant or an adolescent after an episode of distress). The third is pictures of complicity (ie, joyful moments such as parent-child interaction, and partner or peer interaction). The fourth category is neutral scenes (ie, persons walking along a street or in the subway). Levels of color saturation (50%) and lightness (50%) will be adjusted with Adobe Photoshop (Adobe Photoshop Elements 6.0, Los Angeles, USA). The pictures measuring 11.80 cm in height and 11.50 cm in width will be equiluminant and subtended 10.98° (horizontal) x 11.26° (vertical) of visual angle at a viewing distance of approximately 60 cm. All pictures will be displayed on a black background. Pictures will be pseudo-randomized in blocks. Each block will contain 1 slide with a picture of distress, displayed for 10 seconds, with an inter-stimulus-interval of 2 seconds, followed by 1 slide containing 3 pictures (comfort, joy-complicity, and neutral) presented simultaneously and displayed for 20 seconds. Each block of pictures will be separated by an inter-stimulus interval of 10 seconds (Figure 1).

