#### Statistics

To analyze the quantitative variables, parametric (Student *t*) or nonparametric (Wilcoxon) tests will be used, depending on the distribution of variables. The Shapiro-Wilk test will be used to test the normality of the distributions. Clinical and sociodemographic variables collected at the beginning of the study will be described using the mean (SD) for normally distributed continuous variables, and the median, for non-normally distributed variables. For qualitative variables, the chi-square or Fisher's test will be used to compare proportions between the two groups. Statistical analyses will be conducted and supervised by the Methodology and Biostatistics cell of the Centre of Investigation Clinic (CIC) in Besançon. All data will be analyzed using the SAS application. To estimate the clinical relevance of the findings, Cohen’s effect size (Cohen’s d) will be used for parametric outcomes (large effect ≥ 0.8) and *r* for non-parametric outcomes (large effect ≥.5).

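### Analysing each picture category separately can show an oxytocin effect on looking at comfort pictures, but cannot show that the effect is specific to attachment-related content

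*Protocol article*

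**What the plan says.** Under Eye-Tracking Measurements, the protocol article states that "AOIs will be divided into 4 categories (distress, comfort, joy-complicity, and neutral) and each category will be analyzed separately". Under Statistics it adds: "To analyze the quantitative variables, parametric (Student *t*) or nonparametric (Wilcoxon) tests will be used, depending on the distribution of variables". It gives no arm-by-category term, no difference from neutral and no repeated-measures model.

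The aim is set out under Current Study. The general hypothesis is that "insecurely attached adolescents under IN-OT will process attachment-related emotional information in a more accessible and open way compared to PB conditions". The specific prediction is that "Compared to the PB, IN-OT will increase exploration of distress and comfort pictures". The secondary objective concerns "visual exploration strategies for images eliciting attachment-related emotions (ie, distress and comfort".

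The Stimuli section describes 20 pictures in each of four categories. In each block a distress picture is shown alone for 10 seconds, "followed by 1 slide containing 3 pictures (comfort, joy-complicity, and neutral) presented simultaneously and displayed for 20 seconds". Every comfort picture is therefore seen beside a neutral one, by the same participant, at the same time and for the same duration.

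**The concern.** The general hypothesis is about attachment-related information, and the design supplies a neutral comparison on the same slide as the comfort picture. The stated analysis does not use it. With one between-arm test per category, the only route to a statement about specificity is to set a significant result for comfort beside a non-significant result for neutral. That pairing does not test the difference between the two effects, and with about 27 participants per arm it often arises by chance when the effects are equal.

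If oxytocin merely leads participants to fixate more, or to hold gaze better, on any picture, the plan could still yield a result that reads as a change in attachment processing. In addition, comfort, joy-complicity and neutral compete for the same 20 seconds, so their three fixation-time tests are not independent pieces of evidence.

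**Working it through.** **Inputs from the protocol.** The sample-size section gives a difference of 5, SD 6.2, one-sided 5% and 90% power. The normal-approximation calculation returns 27 per arm, or 54 in total; 54 / 0.9 = 60 enrolled. The plan's figure reproduces. It belongs to the primary GPACS outcome and serves here only to fix 27 analysable participants per arm. The 5% level is also from that section. The protocol gives no effect size, SD or correlation for gaze.

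**Assumptions.** Scores are normal with unit variance. Oxytocin shifts comfort and neutral by the same d, so there is no category-specific effect. The within-person correlation between the two scores is r. Tests are two-sided at 5%.

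**Step 1: check by hand at r = 0.** The comfort test alone is significant in about 44% of trials at d = 0.5 and 27 per arm. The neutral test has the same power. The probability that comfort is significant and neutral is not is then 0.44 × (1 − 0.44) = 0.246.

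**Step 2: simulation of the two correlated scores (20,000 trials per setting, d = 0.5).**

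| r | comfort significant, neutral not | comfort-minus-neutral contrast significant |
|---|---|---|
| 0 | 24% | about 5% |
| 0.3 | 20% | about 5% |
| 0.6 | 15% | about 5% |

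Over the same correlations, the misleading pattern occurs in about 10% to 16% of trials at d = 0.3 and 13% to 20% at d = 0.7. At r = −0.3, which competition for slide time makes plausible, it is about 29% at d = 0.5.

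**Step 3: all four categories shifted equally (10,000 trials per setting; d = 0.3 to 0.8, r = 0.3 to 0.7, 27 or 30 per arm).** Distress or comfort is significant while neutral is not in about 9% to 31% of trials. The contrasts with neutral reject in 4.4% to 5.6%.

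**Step 4: what the contrast can detect.** If the effect is in comfort only, the difference score has SD √(2(1 − r)), and power is approximately Φ(d / √(2(1 − r)) × √(27/2) − 1.96).
- d = 0.5, r = 0.3: Φ(0.5 / 1.183 × 3.674 − 1.96) = Φ(−0.41) = 34%.
- d = 0.5, r = 0.5: Φ(0.5 / 1 × 3.674 − 1.96) = Φ(−0.12) = 45%.
- d = 0.5, r = 0.7: Φ(0.5 / 0.775 × 3.674 − 1.96) = Φ(0.41) = 66%.
- d = 0.8: 70%, 84% and 97% at the same three correlations.

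The contrast controls the false claim of specificity, but it is not well powered for a moderate effect.

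**The case against.** The strongest reply is that the prediction is worded against placebo, within named categories. A between-arm test for distress and another for comfort answer it. The protocol nowhere says that neutral will be unaffected, and nowhere plans to infer specificity from one significant and one non-significant result. This stands: the per-category tests are not wrong, and making them descriptive would remove the test of the hypothesis as written. What remains is that the general hypothesis attributes the effect to attachment-related information, and no stated test can support that attribution.

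A reader might infer more than the documents support:
- *That joy-complicity is a control.* The protocol never calls it one. Type of Clinical Trial lists all four categories as attachment-related pictures, and joy-complicity includes parent-child scenes. Neutral is not called a control either, but it falls outside the protocol's own narrower list of distress and comfort.
- *That comfort's share of looking time should replace absolute time.* Joy-complicity is in the denominator. If comfort and joy-complicity each gain 1 second, an illustrative share moves only from 6.8/17 = 0.40 to 7.8/19 = 0.41. A share cannot apply to distress, which is shown alone, or to entry time, fixation order or first fixation duration. Its gain in power depends on an assumed SD of total looking time (mean 17 s, share 0.40 with SD 0.08, rise 0.06): about 58% against 77% at SD 2.5 s, but 73% against 77% to 78% at SD 1 s.

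Two further points have some force. A general rise in fixation time has limited room. Under those same figures (total-time SD 2.5 s) comfort time has SD about √((17 × 0.08)² + (0.40 × 2.5)²) = 1.69 s, so d = 0.5 is about 0.84 s; for three pictures that is 2.5 s of the 3 s left on the slide. The equal-shift scenario therefore fits numbers and durations of fixations better than total time. Also, neutral is analysed too, so a large general effect might be noticed; at this sample size it would often be missed.

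An analysis plan not shown could add the contrast. But the protocol is not silent here: it states separate analysis, and the plan would have to go beyond that wording.

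**Conclusion.** The concern holds in a limited form. The stated analysis can support an oxytocin-placebo difference for comfort pictures, but not a claim that it is specific to attachment-related content. Under an equal shift in comfort and neutral (d = 0.5, 27 per arm, r from 0 to 0.6), the misleading pattern arises in about 15% to 24% of trials, against about 5% for a direct contrast. The size rests on assumed effects and correlations; the logical gap does not. The outcome is secondary and the primary GPACS analysis is unaffected, so this is an improvement worth making and not a flaw in the trial's main result.

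**What to change.** - Keep the between-arm tests for distress and for comfort, which answer the prediction as worded.
- In Eye-Tracking Measurements or Statistics, add one prespecified between-arm test of the within-participant comfort-minus-neutral difference on the three-picture slides, for fixation time and for number of fixations. This is equivalent to an arm-by-category term for those two categories.
- Allow a claim of an attachment-specific effect for comfort only if that contrast supports it.
- Comfort's share of on-picture time may be reported as supportive, noting that joy-complicity is in its denominator.
- Read any distress-versus-neutral contrast cautiously. Distress is shown alone for 10 seconds and neutral beside two other pictures for 20, so the display formats differ, although they are the same in both arms.

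The cost is wording and one extra comparison on data already recorded. The claim becomes narrower if the effect proves general. With 34% to 66% power for a comfort-only effect of d = 0.5, a non-significant contrast should be reported with its confidence interval and not as evidence that the effect is general.

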### Neurophysiological Measurements

EDA will be measured by skin conductance level (SCL) and SCRs. The SCR will be defined as the maximum change in conductance (in µSiemens) in the 0.1 to 6 second window after stimulus onset. The change in neurophysiological response will be calculated by subtracting mean levels of neurophysiological response SCRs (ie, latency and amplitude) during the baseline from mean levels during each slide viewing, a practice commonly used in neurophysiological research [65,67]. HR will be calculated from the R-R intervals in the ECG.

### Procedure

First, a psychologist will evaluate the participant’s diagnostic eligibility. Attachment style will be determined using the ASI [74]. Participants who are classified as insecurely attached will return 1 week later for the OT trial (see Figure 2). Randomization will be centralized and performed after the inclusion of the eligible participants. Participants will be randomly assigned to receive either OT or PB intranasally, with both investigators and participants blind to condition. The randomization code will be kept secret by the pharmacy responsible for dispensing the corresponding medication. To reduce bias, randomization will be performed in blocks, with stratification for confounding factors (eg, age). Experiments will be conducted in a comfortable laboratory during the mid-afternoon hours, in accordance with previous research suggesting stability in the diurnal cycle of plasma OT [84]. Each adolescent will first be asked to choose a topic of disagreement to discuss during the parent-adolescent interaction. Then, 45 minutes before the interaction, the adolescent will be instructed to sit and self-administer 1 puff every 30 seconds, alternating nostrils. The adolescent will take each dose in front of the investigator, to assure correct administration and tolerability. The dosage and timing of the nasal spray administration were chosen based on published research on IN-OT, behavior, and emotions in humans [85], and results on cerebrospinal fluid levels after intranasal vasopressin administration [86]. Dyadic interaction will consist of a 5-minute free conversation and a 10-minute conflict discussion that will both be videotaped. The entire interaction session will be transcribed verbatim, and then coded offline for verbal interaction behavior with the GPACS by coders blind to the study hypotheses. After the dyadic stressful interaction, the adolescent will then be isolated in the ET room for 15 minutes, in order to adapt to experimental conditions. The adolescent will be seated in front of the screen in a comfortable viewing position. After this adaptation phase, the EDA electrodes will be fastened to the second phalanges of the index and middle fingers of the non-dominant hand and 2 ECG electrodes will be placed in a bipolar configuration on interior sides of the participant’s wrists [87]. The RED will perform a 9-point calibration procedure. Once this calibration has been successfully accomplished, the 3 minute baseline responses will be recorded with the BIOPAC system. The participant will be informed that the test is due to start, and that he will freely observe a series of 80 pictures. The neurophysiological monitoring AcqKnowledge 4.3 software will be synchronized with Experiment Center 3.0 (RED SMI) software by event markers representing the beginning of each picture. The participant’s eye movements and neurophysiological recordings (EDA and HR) will begin when the first red dot (approximately 0.95° of visual angle) appears. The task will last for about 15 minutes.
